### 9.2.3 Health economic analysis

A full health economic analysis will be conducted to determine the relative cost-effectiveness of the alternative management approaches.

## 9.3 Sample size

As the strategy of PI monotherapy is likely to offer a major advantage in terms of cost (approximately 50% cost reduction from standard-of-care) and possible advantages in terms of long-term tolerability compared to standard-of-care, the trial aims to demonstrate that PI monotherapy is non-inferior to the standard-of-care by a pre-defined amount in terms of the primary endpoint (non-inferiority trial).

The estimation of the sample size is based on the following assumptions using a time-to-event analysis (29):

1. 97% of patients on the standard-of-care arm will maintain all future drug options (i.e. remain free of new resistance mutations) over three years. This figure is based on an approximate 1% annual incidence of the primary study endpoint in three trials of monotherapy – the OK-04 trial (Pulido F et al, AIDS 2008), the MONET trial (Arribas J et al, AIDS 2010) and the MONOI trial (Katlama C et al, 5th IAS Conference 2009).
2. The PI monotherapy arm will be considered “non-inferior” if the upper limit of the 95% confidence interval (2-sided) for the difference in the proportion of patients who maintain all future drug options over three years (standard-of-care – PI monotherapy) is less than 10%. This is consistent with the majority of HIV non-inferiority trials that use a cut-off of 10-15% and with FDA guidelines which recommend a cut-off of 10-12% (28, 31).
3. 85% power to detect non-inferiority according to criterion 2.
4. Recruitment occurs at a uniform rate over 24 months.
5. Total trial duration of 60 months.
6. Cumulative loss to follow-up is approximately 10% by 5 years.

Under these assumptions a total of 554 patients (277 per arm) are required which has been rounded up to 560.

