## 2.3 Previous trials of PI monotherapy

Four randomised controlled trials of PI monotherapy were presented as abstracts at the 16th World AIDS Conference in Toronto in August 2006, two of which have been recently published in full in a peer-reviewed journal. Three of these trials investigated switching to lopinavir monotherapy after patients had gained full virological suppression using triple-therapy. The largest of these studies, OK 04, enrolled 205 patients who were stable on triple-therapy and randomised them to switch to triple-therapy with lopinavir, or lopinavir monotherapy. Monotherapy was found to be non-inferior (defined with a non-inferiority margin of 12%) to triple-therapy at 48 weeks based on proportion with VL >500 copies/ml. The majority of patients (89%) maintained viral suppression without the need for re-induction and only two patients in this study developed primary PI mutations (4). The data for 96 weeks of follow-up were presented at the European AIDS Conference in October 2007, and showed that lopinavir monotherapy continued to be non-inferior to continuing triple-therapy, with no further virological rebounds with PI resistance. The percentage of patients without therapeutic failure was 87% in the monotherapy arm and 78% in the triple-therapy arm, and there were significantly fewer adverse events in the monotherapy arm (5). In the second study (M03-613) presented in Toronto, 155 treatment-naïve patients were randomised to induction with 2 NRTIs plus lopinavir, followed after 6 months by lopinavir monotherapy versus standard-of-care 2 NRTIs and a NNRTI. There was no significant difference in the rate of maintaining VL <50 copies/ml in the two groups through 96 weeks. Although intermittent increases in VL were seen often in the monotherapy arm, most returned to <50 copies/ml spontaneously and only 4 patients required re-introduction of NRTIs. Two patients treated in the monotherapy arm developed PI resistance mutations (6). The third study, KalMo, randomised 60 patients on stable combination therapy and with undetectable VL to continue existing ART or to receive lopinavir monotherapy. There was no difference in the proportion of patients who maintained undetectable VL in the two groups at 48 weeks (83% in standard-of-care and 86% in monotherapy), and none of the patients in the PI monotherapy arm developed resistance mutations (7). Taken together these 3 randomised controlled trials suggest that switching to lopinavir monotherapy is a viable treatment option in patients who have been already established on stable triple-therapy.

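### The 85% power in section 9.3 does not belong to the non-inferiority rule it is attached to: that rule has over 99.9% power at 277 per arm, and 554 is reproduced only on an unstated hazard-ratio scale

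*Combined protocol and SAP*

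**What the plan says.** Section 9.3 of the protocol assumes that "97% of patients on the standard-of-care arm will maintain all future drug options (i.e. remain free of new resistance mutations) over three years", a figure it takes from an "approximate 1% annual incidence of the primary study endpoint in three trials of monotherapy". It gives no separate rate for the monotherapy arm.

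Criterion 2 calls monotherapy non-inferior if "the upper limit of the 95% confidence interval (2-sided") for the difference in the proportion keeping all drug options "over three years (standard-of-care – PI monotherapy) is less than 10" per cent. The section then claims "85% power to detect non-inferiority according to criterion 2" and concludes: "Under these assumptions a total of 554 patients (277 per arm) are required which has been rounded up to 560". The calculation is described as time-to-event, citing reference 29, with uniform accrual over 24 months, 60 months in total and about 10% loss by five years. No formula and no hazard-ratio margin are printed.

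The margin is supported by precedent: "This is consistent with the majority of HIV non-inferiority trials that use a cut-off of 10-15" per cent, and by FDA guidance of 10 to 12%.

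Section 9.5.1 plans Kaplan-Meier plots and Cox regression for the primary comparison. It does not say which of them yields the interval that decides non-inferiority.

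**The concern.** The power statement points explicitly to criterion 2, and criterion 2 is an absolute difference in three-year proportions. At a 3% risk such a difference is estimated very precisely by 277 patients per arm, so 85% looks far too low. If the number really came from a hazard-ratio calculation, section 9.3 describes one test and powers another.

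The two tests can disagree on the same data, and nothing in section 9.5.1 settles which one governs. The primary conclusion of the trial could then depend on a choice made after the data are seen.

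The near-certain power on the absolute scale also shows how wide 10 points is here: the margin sits at 13% against 3%. The precedents that the protocol describes concern viral load. One is introduced as "Monotherapy was found to be non-inferior (defined with a non-inferiority margin of 12%) to triple-therapy at 48 weeks based on proportion with VL" above 500 copies/ml. In section 2.3, 13% and 22% of the two arms of that trial had therapeutic failure by 96 weeks, and in another trial 14% to 17% had not maintained undetectable viral load at 48 weeks. The endpoint here is resistance, expected in 3%.

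**Working it through.** **Inputs (section 9.3).** Control risk 3% at three years; margin 10 points; two-sided 95% interval (z = 1.96); power 85% (z = 1.036); 277 per arm; accrual 24 months; total 60 months; loss about 10% by five years. *Assumption:* monotherapy risk is also 3%, because no other value is given.

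**1. Reproducing 554.** Convert the margin to a hazard ratio: 97% against 87% gives ln 0.87 / ln 0.97 = 4.57.

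- Freedman events: [(1.96 + 1.036) × (4.57 + 1)/(4.57 − 1)]² = 21.8, so 22.
- With exponential survival, 24 months' uniform accrual, 60 months in total and no loss, the event probability is 0.0398. Then 22/0.0398 = 553 patients, or 277 per arm; power at 554 is 85.3%.
- With the stated loss, 554 patients yield 21.1 events and power is 83.8% (577 patients needed).
- Schoenfeld events: 4 × (1.96 + 1.036)² / (ln 4.57)² = 15.5, so 16. With follow-up cut at three years and loss included, the event probability is 0.0291, giving 550 patients; power at 554 is 86.2%.
- Schoenfeld with the full 36 to 60 months of follow-up does not match: about 420 patients, with 93.7% power at 554.

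So 554 at about 85% is a hazard-ratio result. Which formula was used is inferred.

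**2. Criterion 2 as written.** Sample size per arm: (1.96 + 1.036)² × 2 × 0.03 × 0.97 / 0.10² = 52.3, so 53.

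Power, by exact enumeration of two binomials with 3% risk in each arm:

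| Per arm | Wald interval | Newcombe interval |
|---|---|---|
| 277 | 99.9995% | 99.9985% |
| 249 (277 less 10%) | 99.998% | 99.993% |

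**3. The same data on both scales.** Take 8/277 (2.9%) on control and 24/277 (8.7%) on monotherapy.

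- Risk difference: 5.8 points. The 95% interval is 1.9 to 9.6 (Wald) or 1.9 to 9.9 (Newcombe). The upper limit is below 10, so the result is non-inferior. The lower limit is above zero, so monotherapy is significantly worse.
- Hazard ratio, approximated by the event ratio: 24/8 = 3.0. The standard error of the log is √(1/24 + 1/8) = 0.408, so the upper limit is 3.0 × exp(1.96 × 0.408) = 6.7. This exceeds 4.57, so the result is not non-inferior.

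**4. How often harm passes on the risk difference.** With true risks of 3% and 9%, non-inferiority is declared with probability 47% (Newcombe) to 52% (Wald) at 277 per arm, and 43% to 49% at 249.

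**5. A 5-point margin, same rule.** Ranges run from Newcombe to Wald.

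| Monotherapy risk (control 3%) | Per arm | Power |
|---|---|---|
| 3% | 277 | 89% to 93% |
| 3% | 249 | 85% to 89% |
| 4% | 277 | 66% to 73% |
| 5% | 277 | 39% to 46% |

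**The case against.** The strongest reply is that section 9.3 says the calculation is time-to-event and lists accrual, duration and loss, which only such a calculation needs. On that footing 554 at 85% is reproduced, and the method sits in reference 29, which is not available here. A reader might infer that the 85% is simply an arithmetic error; the documents do not support that. What stands against the reply is that a time-to-event method can also estimate a three-year difference, so those words do not move criterion 2 off the absolute scale, and no hazard-ratio margin is written anywhere.

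A reader might also infer that a tripling of resistance would be called non-inferior. That holds only on the risk-difference reading, and the example is borderline: observed rates of 9% and 3% give a Wald upper limit of 9.92 points at 277 per arm but 10.14 at 249. With 8 control events at 249 per arm, at most 21 or 22 monotherapy events pass. The probabilities in step 4 are less fragile, since loss lowers them only slightly.

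Third, a reader might conclude that the margin must be halved. Nothing in the documents supports 5 points specifically. Section 9.3 offers a trade-off, with about half the cost and possibly better tolerability, and section 2.2 contemplates accepting some risk of failure. Non-inferior and significantly worse can coexist under any wide enough margin, so that coexistence does not prove a power error. It does call for a reporting rule, and the trade-off argument never says why 10 points is acceptable when 3% is expected.

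**Conclusion.** The concern holds as a mismatch of scale. The stated 85% is not the power of criterion 2, which exceeds 99.9% at 277 per arm with or without 10% loss. It is close to the power (84% to 86% in the variants that reproduce 554) of a different test, with a hazard-ratio margin of 4.57 that the plan does not state. Because section 9.5.1 leaves the deciding scale open, identical data can pass or fail.

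This rests on equal 3% risks for the power figures, on exponential survival for the hazard-ratio conversion, and on an inferred event formula. Section 9.3 also justifies 10 points only by precedent and a general trade-off, not against the 3% risk it assumes.

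**What to change.** 1. State in sections 9.3 and 9.5.1, and in the full SAP that section 9.5 promises before analysis, which scale decides non-inferiority.
2. Restate the power to match. For the three-year risk difference as criterion 2 is written, it is over 99.9%, with the interval method named. For a hazard ratio, write the margin of 4.57 into the criterion, name the formula, and quote about 84% to 86%.
3. Add that a result whose interval lies below the margin but excludes zero in favour of control will be reported as significantly worse.
4. Justify the 10-point margin against the 3% expected resistance risk.

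The Trial Steering Committee may consider a 5-point margin as an option, with the power loss in step 5 of the working set out. It is not a required change, and altering a primary margin in an open-label trial already at protocol version 4.0 is more than a wording edit.

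Items 1 to 4 cost text and committee sign-off, with no extra patients. Keeping criterion 2 on the risk difference is the smaller change. Choosing the hazard ratio alters the written criterion and gives up the near-certain power.

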## 9.4 Interim monitoring and analyses

An Independent Data Monitoring Committee (IDMC) will be established to monitor the trial. A charter for the IDMC will be developed prior to starting the trial. The IDMC will meet once before the start of the trial, once within one year of start of recruitment, and at yearly intervals thereafter. In addition to the scheduled meetings, an IDMC meeting may be requested by IDMC members, the Chief Investigator or the Trial Steering Committee at any time. The IDMC will also review safety data at each meeting, and may make recommendations about the conduct of the trial should any safety concerns be identified.

## 9.5 Analysis plan

A full statistical analysis plan will be developed before the trial is analysed. It will be based on the following summary:

### 9.5.1 Primary analysis

The primary analysis will compare the two groups as allocated (intention to treat, ITT) in terms of loss of future drug options (see precise definition of primary outcome measure, above). Time-to-event methods (Kaplan-Meier plots and Cox proportional hazard regression) will be used for this comparison. Although non-inferiority trials often place special emphasis on a per-protocol analysis, this is less relevant for a strategy trial (such as this) than for an explanatory trial comparing the therapeutic efficacy of two drugs. However, we will conduct a sensitivity analysis excluding patients who switch from their randomised allocation within 3 months where this is due to personal preference rather than any clinical indication. In both ITT and per-protocol analyses patients who have died or who are lost to follow-up will be censored at their last viral load measurement. If non-inferiority is demonstrated, an analysis for superiority of the PI monotherapy arm will be performed.

### 9.5.2 Secondary analyses

The primary analysis will be extended to tabulate individual ART drug options and ART class options which are lost due to the development of resistance. Time-to-event methods will be used to analyse the rate of serious drug- or disease-related complications and for viral load rebound. Also, the frequency of grade III and IV adverse events will be tabulated by body systems and randomised group and the groups will be compared using the  $\chi^2$  test. Repeated measures analysis will be used to compare change in CD4+ cell count from baseline in the allocated strategies.

Patient responses on the MOS-HIV questionnaire will be converted to scores on 11 subscales, ranging from 0 to 100, with higher scores indicating better health (32). The scores are then synthesised into a physical health summary score (PHS) and a mental health summary score (MHS). A general linear mixed model will be used to compare the two groups in terms of changes from baseline in the summary PHS and MHS quality of life indexes over the follow-up period.

The scores on each of the neurocognitive tests will be standardised using demographic-adjusted normative means. This procedure will adjust the data for gender, age, level of education and ethnic background. Briefly, standard scores will be calculated by subtracting the appropriate normative mean from the raw score and then dividing by the appropriate normative standard deviation to give a z score (33). The patient's individual z scores on each test will be averaged to give the patient's neurocognitive function summary score at each

visit. A general linear mixed model will be used to compare the two groups in terms of changes from baseline in the neurocognitive function summary score.

Changes from baseline in the 10-year cardiovascular risk score will also be compared between the two groups using a general linear mixed model.

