## 7. ASSESSMENTS & FOLLOW-UP

### 7.1 Routine Follow-up

The main part of the trial will run for 5 years, with recruitment being completed within the first 12-18 months. All patients will continue follow-up visits to a common closing date. After this final visit, data on a few key parameters will continue to be collected by annual retrospective review of the patients' routine clinic visit records for a period of up to 5 years.

The assessments are listed in the trial schedule (see section 1.3). Trial visits and assessments will correspond closely to routine clinical care, with 12-weekly visits throughout the trial. Patients randomised to the PI monotherapy arm will have additional visits at Week 4 and Week 8. Additional visits for VL testing will be required at 4-12 weeks following any VL result  $\geq 50$  copies/ml (see section 7.1.6). Data will be entered on the CRF at each visit.

#### 7.1.1 Week 4

This visit is only required for patients randomised to the ***PI monotherapy arm***.

The visit window is  $\pm 2$  weeks from the target visit date. The visit will be scheduled to occur in the morning due to the requirement for fasting blood tests. Patients should be instructed to not eat or drink anything (except plain water) from midnight before the visit. They should be instructed not to take any morning dose of PI medication (other medication can be taken) until after the blood has been drawn. The following assessments will be performed:

- Review of symptoms
- Review of concomitant medications
- Adherence to ART (no. of missed doses in previous 2 weeks and since last visit)
- Targeted physical examination (as needed to evaluate reported symptoms)
- Review of healthcare resource utilisation since last visit (patient self-report and review of case sheet)
- EQ-5D health status questionnaire
- Laboratory tests:
  - HIV viral load
  - Full blood count (haemoglobin, white cells, neutrophils, lymphocytes and platelets)
  - Biochemistry (sodium, potassium, urea, creatinine, bilirubin, ALT, alkaline phosphatase)
  - Fasting glucose
  - Fasting lipids (total cholesterol, triglycerides, LDL, HDL)
  - PI drug concentration (trough level preferred, or at least 4 hours from last dose)
  - Plasma storage (1 X 4ml EDTA sample)

#### 7.1.2 Week 8

This visit is only required for patients randomised to the ***PI monotherapy arm***.

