#### 9.2.2 Secondary outcome measures

- **Serious drug or disease-related complication**

Defined as the first occurrence of one of the following in any individual patient:

- **Death from any cause**
- **Serious AIDS-defining illness** (see diagnostic criteria, Appendix 7)
- **Serious non-AIDS defining illness** (see diagnostic criteria, Appendix 8)
  - Acute myocardial infarction
  - Coronary artery disease requiring invasive procedures
  - Cirrhosis
  - Acute liver failure
  - End-stage renal disease
  - Stroke
  - Clinical acute pancreatitis
  - Severe lactic acidemia
  - Severe facial lipoatrophy
  - Severe peripheral neuropathy
  - Non-AIDS malignancy

- **Adverse events**

Defined as the total number of Grade III and IV adverse events.

- **Confirmed Virological rebound**

Defined as 3 consecutive VL tests  $\geq 50$  copies/ml, with at least 4 weeks between the first and last test. One of these 3 tests may be a repeat of the same sample. There are a number of alternative definitions for virological rebound, each of which has advantages and limitations (28). The alternative definitions to be used in this trial will be described in the full statistical analysis plan.

- **CD4+ count change**  
Defined as change from baseline in absolute CD4+ count.
- **Health-related Quality of Life change**  
Defined as change from baseline in the mental and physical health summary scores.
- **Neurocognitive function change**  
Defined as change from baseline in the neurocognitive function summary score.
- **Cardiovascular risk change**  
Defined as change from baseline in the risk of cardiovascular disease calculated from the Framingham equation (19).
- **Health care costs**  
Defined as the total cost of health care resources utilised per patient year.

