#### (d) Notification

***Please also refer to the safety reporting flowchart on the following page***

All AEs/ARs, whether expected or not, should be graded using the toxicity table in Appendix 6 and should be then recorded in the toxicity (symptoms) section of the appropriate visit CRF. If the event is grade 3, 4 or an SAE an Event CRF should be completed. This should be sent to the MRC CTU within one working day of the site becoming aware of the SAE or within one month of the grade 3 or 4 event. .

Adverse drug reactions to licensed PIs will continue to be reported by the investigator to the Yellow Card Scheme run by the MHRA and Commission on Human Medicines.

Investigators should record all SAEs occurring from the time of randomisation until 30 days after the last trial visit.

A Safety Reporting Flowchart (Figure 2) is given at the end of this section to help explain the classification and reporting of events. Any questions concerning this process should be directed to the MRC CTU in the first instance. The notification procedure is as follows:

1. The Event CRF must be completed by the investigator (clinician named on the Delegation of Authority log who is responsible for the patient's care), with due care being paid to the grading, causality and expectedness of the event as outlined above. In the absence of the responsible investigator, the form should be completed and signed by a member of the site trial team. The responsible investigator should subsequently check the Event CRF, make changes as appropriate, sign and then re-fax to the MRC CTU as soon as possible. The initial report shall be followed by detailed, written reports as appropriate.
2. Send the Event CRF by fax to the MRC CTU, fax number: [name].
3. Follow-up: Patients must be followed-up until clinical recovery is complete and laboratory results have returned to normal or baseline, or until the event has stabilised. Follow-up should continue after completion of protocol treatment if necessary. Follow-up information for the event should be noted on a new Event CRF by ticking the box marked 'follow-up' and faxing to the MRC CTU as information becomes available. Extra, annotated information and/or copies of test results may be provided separately. The patient must be identified by trial number, date of birth and initials only. The patient's name should not be used on any correspondence. A new Event CRF should be completed for the final report.

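### Grade III/IV adverse events are defined as a total event count, but the chi-squared comparison states no unit; applied to that count, its type I error exceeds 5% whenever events cluster within patients

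*Combined protocol and SAP*

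**What the plan says.** Section 9.2.2 gives the adverse event outcome in one line: "Defined as the total number of Grade III and IV adverse events". The unit is the event.

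Section 9.5.2 then states that "the frequency of grade III and IV adverse events will be tabulated by body systems and randomised group and the groups will be compared" by a chi-squared test. It does not say what is counted in the cells of the table.

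The neighbouring outcome, serious drug- or disease-related complications, does fix its unit: "Defined as the first occurrence of one of the following in any individual patient". Section 9.5.2 assigns it time-to-event methods. Adverse events have neither a per-patient definition nor an analysis that uses follow-up time.

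On recording, section 11.2.1(d) says: "If the event is grade 3, 4 or an SAE an Event CRF should be completed". One patient can therefore contribute several events. The same section has later information on an event sent on an Event CRF marked as follow-up.

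On visits, section 7.1 says: "Patients randomised to the PI monotherapy arm will have additional visits at Week 4 and Week 8".

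On the status of the text, section 9.5 says: "A full statistical analysis plan will be developed before the trial is analysed". It adds that the full plan is to rest on the summary given there.

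**The concern.** A chi-squared test needs independent units. Patients are independent; two events in the same patient generally are not, because some patients are more prone to toxicity than others. If events are counted as though each came from a different patient, the variance is understated and the p-value is too small. The test also takes no account of how long each patient was observed.

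The comparison matters because safety and toxicity form the second trial objective (section 2.4.1), and better tolerability is part of the case for PI monotherapy (sections 1.1, 2.5.5 and 9.3). A spuriously small p-value could point in either direction.

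A second, smaller matter is that only the PI arm is seen at Weeks 4 and 8, which gives that arm some extra opportunity to have an event recorded.

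**Working it through.** **Plan's own figure.** None. The protocol states no event rate, dispersion, significance level or power for this comparison, so there is nothing to reproduce. Event rate and clustering below are assumptions, shown over a range.

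**Inputs from the protocol**
- Unit of the outcome: events (section 9.2.2).
- Test: chi-squared, unit not stated (section 9.5.2).
- Patients: "Under these assumptions a total of 554 patients (277 per arm) are required which has been rounded up to 560" (section 9.3), so 277 to 280 per arm.
- Follow-up: "Total trial duration of 60 months" with uniform accrual over 24 months (section 9.3), so 36 to 60 months per patient before loss.

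**Assumed inputs.** Mean μ = 0.25 to 2 Grade III/IV events per patient; negative binomial dispersion k = 0 to 3; no true difference between arms; two-sided nominal 5%.

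**Formula.** Let a and b be the total events in two equal arms of n patients. The event-level statistic is X² = (a − b)²/(a + b) on 1 df. Its denominator estimates 2nμ. The true variance of a − b is 2nμ × V, where V = 1 + kμ is the variance-to-mean ratio of events per patient. X² therefore behaves as V times a chi-squared variable on 1 df, and

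type I error = 2 × [1 − Φ(1.96/√V)].

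The number of patients cancels, so 277 or 280 per arm makes no difference.

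**Numbers.** At μ = 0.5 and k = 1, V = 1 + 1 × 0.5 = 1.5; 1.96/√1.5 = 1.600; error = 0.110. Other settings, with a simulation check (10,000 trials per setting, 280 per arm):

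| μ | k | V | Formula | Simulated: events | Simulated: patients with ≥1 event | Simulated: mean count, clustered variance |
|---|---|---|---|---|---|---|
| 1 | 0 | 1.00 | 0.050 | 0.050 | 0.051 | 0.051 |
| 0.25 | 1 | 1.25 | 0.080 | 0.082 | 0.052 | 0.054 |
| 0.5 | 1 | 1.50 | 0.110 | 0.109 | 0.049 | 0.050 |
| 1 | 1 | 2.00 | 0.166 | 0.171 | 0.050 | 0.054 |
| 1 | 2 | 3.00 | 0.258 | 0.257 | 0.052 | 0.049 |
| 2 | 3 | 7.00 | 0.459 | 0.447 | 0.044 | 0.045 |

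The last row is the extreme of the grid, not a prediction. Over the whole grid the per-patient test ran at 0.044-0.052 and the mean-count test with clustered variance at 0.045-0.054.

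**Single body systems.** At an assumed μ = 0.1 with k = 1 to 2, V = 1.1 to 1.2. Then 1.96/√1.1 = 1.869 gives 0.062, and 1.96/√1.2 = 1.789 gives 0.074. The error is about 6-7%.

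**Follow-up time alone.** Follow-up uniform on 3 to 5 years has mean 4 and variance 2²/12 = 0.333, so a squared coefficient of variation of 0.333/16 = 0.021. At μ = 1 with no other clustering, V = 1.021 and the error is about 5.2%. Staggered entry by itself adds little; clustering of events within patients is what matters.

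**Extra visits.** The schedule in section 1.3 and sections 7.1.1 and 7.1.2 give PI-arm patients symptom review at both Weeks 4 and 8. Blood count, chemistry, fasting glucose and lipids are taken at Week 4 only. All patients have symptom review and these bloods at Week 12 (section 7.1.3).

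**The case against.** The strongest reply is that section 9.5.2 never says events are the test units. *Frequency* may well mean patients with an event, which is what a chi-squared test normally compares, and on that reading the test holds its size. That stands, and it rules out saying flatly that the planned p-values are too small. It does not settle the matter, because a per-patient test does not analyse the total count that section 9.2.2 defines.

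The sponsor can also point to the full analysis plan still to be written. That lowers the urgency, but that plan is to be built on this summary.

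Three stronger readings are tempting and are not supported:

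- *A persistent laboratory abnormality is counted again at each visit.* Section 11.2.1(d) has an event followed until it resolves or stabilises, with later reports marked as follow-up. It is one event. Distinct and recurrent events in one patient can still cluster.
- *Two extra visits on about 17 twelve-weekly visits over four years give the PI arm 12% more chances to record any event.* Week 8 has no safety bloods, so for laboratory events the extra is one visit in about 17. Extra visits add no time at risk, and an abnormality still present at Week 12 would be found in both arms. Any tilt runs against PI monotherapy.
- *Events found at Weeks 4 and 8 should be excluded.* That would remove events from the PI arm only, including early toxicity of newly started PIs, while control events from the same weeks reported at Week 12 stayed in. It would add bias.

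**Conclusion.** The point holds as a mismatch between sections 9.2.2 and 9.5.2. Either the test is run on the outcome as defined, and its type I error exceeds 5% whenever events cluster within patients, or it is run on patients, and the defined outcome goes unanalysed. One of the two sections must change.

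The size is illustrative. Under assumed negative binomial counts it is about 8% at a mean of 0.25 events per patient (variance inflation 1.25), 11% at 0.5 (inflation 1.5) and 17-26% at 1 (inflation 2-3). It is smaller within single body systems and 5% with no clustering. A reader should not take any of these as the trial's actual error rate, because the documents give neither an event rate nor a dispersion.

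The Week 4 and 8 visits create some unequal ascertainment, which is a secondary matter. Serious complications, the other main safety outcome, are already defined per patient. The primary non-inferiority conclusion and the sample size are not affected.

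**What to change.** Make sections 9.2.2 and 9.5.2 agree, and carry the wording into the full analysis plan:

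1. Compare the number of patients with at least one Grade III/IV event, overall and by body system, by chi-squared test.
2. Compare total Grade III/IV events as a rate, by negative binomial regression (or a rate model with robust variance) with log follow-up time as offset.
3. State that follow-up reports of a continuing event do not count as new events.
4. If the effect of the PI-only visits is to be explored, add a sensitivity analysis that treats both arms alike, such as laboratory events at visits common to both arms. Do not exclude Week 4 and 8 events from the PI arm alone.

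The cost is a few lines of text and minor programming. Event reports and follow-up dates are already collected. The one statistical downside is slightly wider intervals for the total-event comparison than a test that ignores clustering would imply.
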